### 10.3. Sample Size Determination

Based upon I-HaND data for patients with hand nerve conditions and our recent sample of digital nerve patients, the standard deviation (SD) could be as high as 21 points (23). To detect a target mean difference of 7 points (previous work in a similar measure suggests 7 would be an important difference; 0.3 standardised effect size) in the I-HaND with an SD of 21, 2-sided 5% significance level and 90% statistical power, 191 participants will be required per group (382 overall) (14, 27, 28). Based on the team's experience of other digital nerve studies and hand trials 20% missing data has been allowed for giving an overall target of 478.

### 10.4. Analysis populations

All participants will be grouped according to their randomly allocated group (i.e. intention to treat/treatment policy) in the principal analyses. Complication data may also be presented (but not formally compared) by treatment received.

### **10.5. Decision points**

No formal stopping rules are incorporated into the design and sample size, and accordingly no formal interim analyses are planned. The pilot phase will only assess trial feasibility, not clinical outcomes. An independent DMC will meet early in the course of the study to agree its terms of reference and will review confidential interim reports of accumulating data.

### **10.6. The Level of Statistical Significance**

Statistical significance will be at the 5% level with corresponding confidence intervals derived whenever possible. Subgroup analyses will be at the same significance level but will be labelled “exploratory”.

### **10.7. Procedure for Accounting for Missing, Unused, and Spurious Data.**

Principal analyses will be based upon observed data without imputation. The impact of missing data will also be explored in sensitivity analyses of the primary outcome and key secondary outcome (EQ-5D-5L) utilising using appropriate methods (e.g. the `rctmiss` Stata command for assessing the impact of missing not at random using a pattern mixed-model based approach) (29, 30).

### **10.8. Health Economics Analysis**

An economic evaluation alongside the randomised controlled trial will be performed at 12-months post randomisation. The economic evaluation will be carried out on an intention-to-treat basis, from a NHS and personal and social services perspective including medical costs attributable to the digital nerve injury. Total costs and Quality Adjusted Life Years (QALYs) for both groups will be estimated. The mean differences in costs and QALYs between the two groups will be estimated using regression analyses controlling for baseline scores and trial stratification variables. The incremental cost-effectiveness ratio (ICER) will be calculated by dividing the difference in costs between the two treatment groups with the difference in QALYs.

The uncertainty surrounding the ICER will be estimated using non-parametric bootstrapping. To illustrate the statistical uncertainty surrounding the ICERs, the bootstrapped cost and QALYs pairs will be plotted on a cost-effectiveness (CE) plane (31). In a CE plane, the incremental costs between the two treatment groups will be plotted on the y-axis and the incremental QALYs on the x-axis. The cost-effectiveness acceptability curves (CEA curves) will be estimated to demonstrate the probability of cost-effectiveness of the two surgical procedures for a range of different willingness to pay thresholds. Following the recommendation from NICE, the treatment will be considered cost-effective when the ICER is less than £20,000 - £30,000 (32).

It is expected that the amount of missing data will be considerable, given the number and nature of healthcare resource use data and the different measurement points. Thus, multiple imputation methods (i.e. multiple imputation by chained equations) will be used for the main analysis to impute missing cost and QALYs data (33).

A number of secondary and sensitivity analyses will be undertaken to check the robustness of the results of the main analysis. A secondary analysis additional health outcomes will be considered, such as the I-

HaND. As a sensitivity analysis, the economic evaluation will be performed from a societal perspective including lost productivity costs, given the importance of returning to usual activities and work to the younger patients with a digital nerve injury. Another sensitivity analysis will be carried out including only complete cases, to explore the impact of multiple imputation on the results.

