## 2. LAY SUMMARY

Digital nerves are small nerves that pass along the side of each finger and provide sensation to the fingertips (see diagram). These nerves can be accidentally cut when handling sharp objects like a knife or broken glass. The NEON study aims to find out whether sewing the ends of the cut nerve surgically is beneficial or even needed. Thoroughly cleaning the cut wound before closing the skin is a much simpler procedure, and may be satisfactory for patients.

[figure not shown]

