|           |                                                                                                                     | 
 
• Static two-point discrimination test (2PD)
 
• Tactile gnosis using Shape/Texture Identification (STI) test
 
• Touch thresholds using Weinstein Enhanced Sensory Test (WEST) monofilaments
 
 | 3 months and 12 months post randomisation (assessed at NEON clinical appointments) |
|           | To examine the cost-effectiveness of microsurgical nerve repair.                                                    | 
 
• Health resource use questionnaires
 
• EQ-5D-5L index
 
                                                                                                                                              | 6 weeks, 3 months, 6 months and 12 months post randomisation                       |
|           | To compare complications of surgery and clinically problematic neuroma rates in the two surgical arms.              | 
 
• Patient reported complication
 
• Clinical assessment (including Elliot score)
 
• Complications and further procedures in medical records
 
                                                  | 3 and 12 months post randomisation                                                 |
|           |                                                                                                                     | Long term followup 
 
• Complications and further procedures based upon medical records and routine data
 
                                                                                                | 24 months post randomisation                                                       |

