### Current Evidence

Clinical uncertainty surrounds the efficacy of digital nerve repair following traumatic digital nerve injury. A systematic review on the outcomes of repair in 2019 included all studies comparing documented surgical digital nerve repair with unrepaired injuries (3). This review highlighted the absence of randomised controlled trials amongst single centre consecutive case series (4). Results of non-comparative observational studies showed that surgical repair led to sensory recovery to pre-injury levels in a minority of patients (24%). Sensory function was determined in most cases by comparison of static 2 point discrimination (2PD) between the injured area and the contralateral, uninjured area. The most frequent primary outcomes assessed were not patient reported, and included assessment of hand function tending towards neurological clinical assessments of finger sensibility, assessed by spatial discrimination and detection threshold. Neither measures truly reflect the functional impact of sensory impairment due to patients adapting behaviour and assessor skill. Notably, in a study where the digital nerve was not repaired, the majority regained protective sensibility by 6 months and all patients declined further surgical intervention to improve their sensibility, suggesting satisfaction with the outcome (5).

A common justification by surgeons to undertake a digital nerve repair is to reduce the rate of nerve injury specific complications, such as neuroma, cold intolerance or other sensory disturbance. This was highlighted in a national survey (6). However, in contrast to the survey results, the systematic review indicates no evidence to support a hypothesis of higher adverse outcomes if a nerve is left unrepaired (neuroma rate 4.6% repaired versus 5% unrepaired) (5, 7-13).

The review also revealed deficiencies in clinician and patient communication. Some clinicians are likely not to be fully informing patients that their finger sensation may not return to pre-injury level, even with repair (14-19).

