## Study Rationale

The limited work in this area highlights the uncertainty around whether there is a benefit to digital nerve repair. Responses from a survey of over 140 surgeons and therapists confirmed the existence of community equipoise. While some respondents stated that microsurgical repair is effective and essential, a considerable number were uncertain of efficacy, and confirmed the need for and willingness to engage with such a trial (6).

The NEON study seeks to answer whether microsurgical digital nerve repair is clinically effective, by comparing two surgical procedures. Given the lack of current evidence, the high frequency of the procedure and the lack of resources in the NHS, a robust trial is required to address the surgical dogma that surrounds this injury and its management.

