## Choice of Treatment Arms

The treatment arms for the study are detailed in section 8.6 and can be summarised as:

- Intervention: Digital nerve surgery with microsurgical sutures
- Comparator: Digital nerve surgery with realignment of nerve ends but no microsurgical sutures

Surgery with microsurgical sutures is the standard practice in the majority of NHS hospitals. Surgery without sutures was chosen as a comparator based on previous studies where the nerve was left unrepaired. Both groups will undergo treatment and some form of surgical operation. Hence the no suture group is not analogous to no treatment. The involvement of a surgical procedure in both groups protects against the known placebo effects of undergoing an operation. The design is therefore more akin to a comparison of two surgical interventions, identical except that one has the suspected critical surgical element omitted. Conducting both treatment arms in theatre allows specialist confirmation of diagnosis and participant blinding. It also allows those with concomitant injuries to have these repaired at the same time as their digital nerve surgery. During the study, the identification and referral of digital nerve injury from A&E will be evaluated (section 8.2). This will facilitate the possible extrapolation of study results into this setting.

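### The ICER rule in Section 10.8 has no condition on the sign of the QALY difference, so it gives the wrong verdict when suturing yields fewer QALYs

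*Protocol*

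**What the plan says.** Section 10.8 obtains the ICER by "dividing the difference in costs between the two treatment groups with the difference in QALYs". Citing NICE, it then sets its one decision rule: "the treatment will be considered cost-effective when the ICER is less than £20,000 - £30,000". The section puts no condition on the sign of the QALY difference, gives no rule for dominance and does not mention net benefit.

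Uncertainty is to be shown graphically: "the bootstrapped cost and QALYs pairs will be plotted on a cost-effectiveness (CE) plane". Acceptability curves are also planned over a range of thresholds. Neither display has a verdict by quadrant attached, and the text does not say how the probability on the curves is computed.

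The sentence does not say which arm is meant by the treatment. The objective in the Synopsis is "To examine the cost-effectiveness of microsurgical nerve repair", and Section 5 labels the arms with "Intervention: Digital nerve surgery with microsurgical sutures". Both point to suturing.

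**The concern.** A ratio of two differences loses the information on which side of zero each difference lies. An upper limit on cost per QALY makes sense when suturing gains QALYs, because a low price for a gain is good. It makes no sense when suturing loses QALYs. The ratio is then either negative (dearer and worse) or a saving per QALY given up (cheaper and worse), and in the second case a low value counts against suturing.

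The protocol's own background makes this more than a formal point. Section 5, Study Rationale, says: "The limited work in this area highlights the uncertainty around whether there is a benefit to digital nerve repair". Current Evidence in the same section reports near-equal complications ("neuroma rate 4.6% repaired versus 5% unrepaired"). The Lay Summary says of the alternative: "Thoroughly cleaning the cut wound before closing the skin is a much simpler procedure, and may be satisfactory for patients". A QALY difference close to zero, with suturing dearer, is therefore one of the results that the trial must be able to interpret. At stake is a prespecified rule that could label a dominated procedure cost-effective.

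**Working it through.** The rule is a criterion, not a computed figure, so there is nothing in the plan to reproduce. The check compares its verdict with that of net monetary benefit.

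**Notation.** ΔC and ΔQ are the cost and QALY differences, suture minus no suture. L is the threshold per QALY (£20,000 or £30,000, from Section 10.8).

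**Algebra.**
- ICER = ΔC / ΔQ, so ΔC = ICER × ΔQ.
- Net monetary benefit: NMB = L × ΔQ − ΔC = ΔQ × (L − ICER).
- If ΔQ > 0, NMB > 0 exactly when ICER < L, and the written rule is right.
- If ΔQ < 0, NMB > 0 exactly when ICER > L, and the written rule is reversed.

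**Worked cases.** The protocol gives no expected cost or QALY difference, so these values are illustrative.

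| ΔC | ΔQ | ICER | Written rule | NMB at £20,000 | NMB at £30,000 | Correct verdict |
|---|---|---|---|---|---|---|
| +£400 | +0.03 | £13,333 | passes | +£200 | +£500 | cost-effective |
| +£400 | +0.01 | £40,000 | fails | −£200 | −£100 | not cost-effective |
| −£400 | +0.01 | −£40,000 | passes | +£600 | +£700 | cost-effective (dominant) |
| +£400 | −0.01 | −£40,000 | passes | −£600 | −£700 | not cost-effective (dominated) |
| −£400 | −0.03 | £13,333 | passes | −£200 | −£500 | not cost-effective |
| −£400 | −0.01 | £40,000 | fails | +£200 | +£100 | cost-effective |

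For the fourth row at £20,000: 20,000 × (−0.01) − 400 = −600. The rule is right in the first three rows and wrong in the last three. In the cheaper-and-worse quadrant it errs in both directions. The same ratio also carries opposite verdicts: £13,333 appears in rows one and five, and −£40,000 in rows three and four.

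One million simulated pairs (ΔC with mean 0 and SD £500; ΔQ with mean 0 and SD 0.02) agreed with the algebra at both thresholds: 0% wrong verdicts with ΔQ > 0 and 100% wrong with ΔQ < 0.

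**How likely is an observed ΔQ below zero?** With true difference d, QALY standard deviation SD and n per arm, the probability is Φ(−d / (SD × √(2/n))). From the protocol, n is 191 (Section 10.3, analysed) to 239 (Synopsis, randomised). The protocol gives neither SD nor d; SD is assumed to be 0.10 to 0.20.

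| Assumed true difference | Chance that observed ΔQ < 0 |
|---|---|
| 0 | 50% |
| +0.005 | 29-40% |
| +0.01 | 14-31% |
| +0.02 | 1-16% |

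As a check on the +0.01 row: with SD 0.10 and n = 239, 0.10 × √(2/239) = 0.00915 and Φ(−0.01/0.00915) = 0.137. With SD 0.20 and n = 191, 0.20 × √(2/191) = 0.0205 and Φ(−0.01/0.0205) = 0.313.

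**The case against.** The strongest reply is that Section 10.8 already plans the displays that reveal the problem. A cost-effectiveness plane shows at once whether the estimate lies on the side of QALY loss, and acceptability curves built on net benefit would not carry the error. A competent health economist would notice. This stands as a reason to rate the point lower. It does not repair the rule: the plane is there to illustrate uncertainty, no verdict is tied to either display, and if the curves were built by counting bootstrap pairs with a ratio below the threshold they would inherit the fault.

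A second reply is that quadrant conventions and dominance belong in an analysis plan. Had the protocol been silent, that would settle the matter. But it states a rule, and the rule as stated gives wrong answers.

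A third reply is that the rule is sound if the treatment means whichever procedure yields more QALYs. That is true, but the sentence does not say so, and the objective and arm labels point to suturing.

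Three stronger readings should be resisted:
- **Half of all results would be misjudged.** This holds only if the true QALY difference is exactly zero; small positive differences give lower figures.
- **The published economic conclusion will be wrong.** Harm would require an analyst to apply the sentence literally beside a plane showing the opposite.
- **The £20,000 to £30,000 range is itself a fault, because an ICER inside it has no verdict.** The protocol states a threshold range and plans curves across thresholds. Reporting at both ends, as proposed here, would also give no single verdict when the ends disagree.

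**Conclusion.** The rule is wrong as written; the consequence is minor to moderate. That it reverses for every negative QALY difference is exact and needs no assumption beyond reading the treatment as suturing. How often this would matter is not known: it rests on a QALY SD and a true difference that the protocol does not give, and the pound and QALY values in the worked cases are illustrative. A QALY difference near or below zero is plausible on the protocol's own account of the evidence. The primary outcome, sample size and data collection are unaffected.

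**What to change.** In Section 10.8, replace the ICER rule with a net-benefit rule: suturing is considered cost-effective if incremental net monetary benefit (threshold × QALY difference − cost difference, suture minus no suture) exceeds 0, reported separately at £20,000 and at £30,000 per QALY with bootstrap intervals. State that the acceptability curves are computed from net benefit. Report any ICER only with its quadrant, and state dominance where it applies.

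This takes about two sentences and uses the bootstrap pairs already planned. It needs no new data and changes no trial procedure.

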## **11. DATA MANAGEMENT**

The data management aspects of the study are summarised here with details fully described in the Data Management Plan.

### **11.1. Source Data**

Source documents are where data are first recorded, and from which participants' CRF data are obtained. These include, but are not limited to, hospital records (from which injury and hand therapy details may be summarised into the CRF), clinical and office charts, laboratory records, diaries, and correspondence.

CRF entries will be considered source data if the CRF is the site of the original recording (e.g. there is no other written or electronic record of data). All documents will be stored safely in confidential conditions. Data from participant questionnaires and from clinical assessments will be made available to sites to ensure the PI holds a contemporaneous copy. On all study-specific documents, other than the signed consent, the participant will be referred to by the study participant number/code, not by name.

### **11.2. Access to Data**

Direct access will be granted to authorised representatives from the Sponsor and host institution for monitoring and/or audit of the study to ensure compliance with regulations.

On completion of the study, and with appropriate participant consent, fully anonymised data may be shared with other organisations at the behest of the funder. All requests for the use of the data from the NEON study will be approved by the CI, Trial Management Group (TMG) and where necessary the Trial Steering Committee (TSC). A data request form should be completed detailing the decision as to whether the request is accepted. In cases where individual site data is requested, only summary data would be provided with caveats for dissemination, to emphasise that study data should be interpreted as a whole.

### **11.3. Data Recording and Record Keeping**

A Data Management and Sharing Plan will be produced for the study, which will describe the methods of data collection, entry and management, including details of data management tools and the study-specific database. All data will be processed in accordance with the Sponsor's policy for data protection.

All study-specific documents, except for the signed consent form and follow-up contact details, will refer to the participant with a unique study participant number/code and not by name. Participant identifiable data will be stored securely in accordance with OCTRU SOPs.

Site teams will enter data directly into the study-specific database, which will be validated and queried by central study team. The central team will control access to the database in accordance with OCTRU SOPs. Any paper questionnaires returned by participants will be stored securely in offices only accessible by swipe card by the central coordinating team staff in Oxford and authorised personnel.

Focus groups will be audio recorded in the field using a digital recording device; the resulting audio files (and accompanying field notes) will be transcribed for storage, and the original file deleted from the recording device, as soon as is practicably possible. Any identifying information appearing in focus group transcripts will be removed as soon as possible following transcription to minimise risk of participant identification. Transcription will be performed by a professional transcribing firm routinely sourced by the University of Oxford and versed in dealing with patient data. A confidentiality agreement will be put in place. Audio files will be treated as identifying data and will be excluded from archiving and sharing.

## **12. QUALITY ASSURANCE PROCEDURES**

The study may be monitored or audited in accordance with the current approved protocol, GCP, relevant regulations and SOPs.

### **12.1. Risk assessment**

OCTRU conducted a risk assessment prior to the study starting. Issues raised have been addressed within the final protocol and procedures have been planned to monitor the ongoing risks of the study. A risk proportionate approach will be utilised within this study. The risk assessment will be reviewed as necessary over the course of the study to reflect significant changes to the protocol or outcomes of monitoring activities.

### **12.2. Study monitoring**

Regular central monitoring of study procedures will be imbedded into the study conduct and management, according to a study specific Monitoring Plan. The study will be subject to audit OCTRU Quality Assurance team, according to its Audit Programme. The study will also undergo a process of review before it is granted the green light to begin recruiting patients.

### **12.3. Study Committees**

The Trial Management Group, Trial Steering Committee and Data Monitoring Committee will be set up and run in accordance to their Charters. All members have to sign to agree to the conditions of the Charter before sitting on a committee.

## **13. PROTOCOL DEVIATIONS**

A study related deviation is a departure from:

- the ethically approved study protocol
- other study document or process (e.g. consent process or administration of study intervention)
- GCP
- any applicable regulatory requirements.

Any deviations from the protocol will be documented in a protocol deviation form and filed in the study master file. OCTRU SOPs will be followed for the procedure of identifying non-compliances, escalation to the central team and assessment of whether a non-compliance/deviation may be a potential serious breach.

